aHUS is an acute disease with many patients presenting with nonspecific clinical symptoms, including fatigue, pallor, shortness of breath, and reduced urine output with or without edema.^2^, ^3^, ^4^ This varying clinical presentation, combined with the absence of diagnostic biomarkers for aHUS leads to difficulty in diagnosing complement-mediated aHUS from other causes of TMA and definitive test results (autoantibodies or genetic testing), which are only positive in approximately 60% of patients, are not typically available for days to weeks after clinical presentation. Therefore, a diagnosis of aHUS remains a clinical one relying on ruling out other forms of TMA,^16^ notably thrombotic thrombocytopenic purpura as well as hemolytic uremic syndrome caused by Shiga toxin-producing *Escherichia coli*. Indeed, other forms of TMA may be due to distinct mechanisms that do not involve complement activation; for example, thrombotic thrombocytopenic purpura, diacylglycerol kinase epsilon pathogenic variants, and methylmalonic aciduria and homocystinuria cblC complementation type do not respond to treatment with the anti-C5 monoclonal antibody eculizumab.^24^^,^^25^ Furthermore, other diseases, such as systemic lupus erythematosus or sepsis, may have clinical and laboratory findings suggesting a diagnosis of TMA. Therefore, one of the challenges of clinical trials involving patients with aHUS is that there is a risk of patients without complement-mediated aHUS being enrolled, which could lead to either a poor response to treatment or spontaneous resolution (“response”) despite inappropriate treatment.^26^, ^27^, ^28^

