### Statistical Considerations

#### Primary Efficacy Estimand

The primary analysis of the primary end point is the assessment of the proportion of patients reaching the status of complete TMA response over 26 weeks (core treatment period). The calculated TMA response rate will be compared with a threshold of 30% using a 2-sided 95% confidence interval (CI) for the proportion of complete TMA responders in iptacopan-treated patients based on asymptotic Gaussian approximation with continuity correction method. The 30% threshold was chosen based on 2 historical trials that are comparable in study design, population, and efficacy endpoints (eculizumab,^36^ ravulizumab^27^). The TMA response rates (and 95% CI) based on asymptotic Gaussian approximation with continuity correction method for the eculizumab and ravulizumab trials were 56.1% (39.7%, 72.5%) and 53.6% (39.6%, 67.5%), respectively. Given the single-arm nature of historical trials, it is difficult to hypothesize the actual extent of eculizumab or ravulizumab effect versus placebo. However, the lower boundaries of the 95% CI (∼40%) could be considered as a demonstrated effect over placebo and taken as the reference. A 30% threshold has been chosen to ensure the preservation of approximately 75% of this reference. A lower bound of the CI of ≥30% will demonstrate that iptacopan preserves a significant proportion of the treatment effect compared to that observed with anti-C5 antibody therapies eculizumab and ravulizumab. The primary analysis will account for different intercurrent events as explained in the following:•Dialysis: if a patient requires dialysis during the 26-week treatment period, creatinine values during dialysis (from first day of dialysis through 5 days after the end of dialysis) will be excluded from the analyses. If a patient is on dialysis throughout the 26 weeks where baseline or postbaseline creatinine values are not available for determining the kidney improvement component of complete TMA response, the patient will be considered a nonresponder. For a patient on dialysis on day 1 (or within 5 days prior), baseline creatinine will be the first assessment ≥6 days postdialysis.•Transfusion: platelet values obtained from the day of a platelet transfusion through 3 days after the transfusion will be excluded from the analyses.•Discontinuation of study treatment for any reason: all available efficacy data will be included to calculate TMA response status without imputation.•Plasma exchange/plasma infusion or anti-C5 antibody therapy use during the treatment period: patients will be considered as nonresponders.

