
The primary analysis will be performed on the full analysis set, which comprises all patients with aHUS (whose eligibility has been confirmed by the patient selection committee) to whom study treatment has been assigned and who have received at least 1 dose of study treatment. The patients discontinued from the study for not meeting the eligibility criteria based on central laboratory or not confirmed to be eligible by the patient selection committee will be excluded from the full analysis set.

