#### Sample Size Determination

The proposed sample size of 50 patients is sufficient to achieve a target absolute margin of error not larger than 0.15 (half-width of a 2-sided 95% CI for the proportion of patients reaching the status of responder) based on asymptotic Gaussian approximation with continuity correction method.

Under the assumption of the true TMA response rate for patients treated with iptacopan being 50%, at 1-sided alpha of 2.5%, the sample size of 50 will provide >80% probability that 2-sided 95% CI will exclude TMA response rate of 30%.

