A novel aspect of the study design is the patient selection committee; the patient selection committee was created for this study to avoid some of the pitfalls of recent clinical trials in aHUS.^27^ Misdiagnosis may occur in complement-mediated aHUS because of patients having other etiologies of TMA, various other genetic disorders, or having diseases such as sepsis or systemic lupus erythematosus that may have similar clinical and laboratory findings. Given the absence of a definitive diagnostic test available at study entry, there have been difficulties in making the diagnosis of aHUS, as illustrated by the recent ravulizumab trials.^27^^,^^38^ Patients in the initial eculizumab trial had a high mutation-positive rate (suggesting a high proportion of complement-mediated aHUS) whereas those in the ravulizumab trial had a low mutation rate, with an increased number of deaths (4 of 58 patients), and a number of patients enrolled who did not appear to have complement-mediated aHUS, and thus are not expected to respond to complement inhibitors.^26^, ^27^, ^28^ Enrolling patients without complement-mediated aHUS can lead to nonresponse to therapy or be a safety concern by administering a drug that is not appropriate for the patient.

Defective complement control on the endothelial surface results in a prothrombotic state in aHUS^2^ with loss and/or gain of function mutations in complement regulatory genes resulting in AP overactivation and impaired C3b degradation. The establishment of the key role of the AP in aHUS pathophysiology highlighted the rationale for complement inhibition as a therapeutic strategy and has resulted in the investigation of several novel targeted agents, such as iptacopan. Whereas most complement therapies target the terminal pathway, iptacopan inhibits the proximal node of the AP, which plays a key role in the amplification of the classical and lectin pathways.^12^^,^^14^

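### The full-analysis-set rule removes already-dosed patients on an eligibility decision that is neither confined to pre-dose information nor masked to response

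*Protocol article*

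**What the plan says.** In the Protocol article, Primary Efficacy Estimand, the full analysis set contains patients confirmed by the patient selection committee who were assigned treatment and took at least one dose. The next sentence takes out patients discontinued because the central laboratory shows that they fail eligibility, or "not confirmed to be eligible by the patient selection committee will be excluded from the full analysis set".

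Study Population gives the committee the task of independently reviewing each diagnosis and confirming enrolment. It sets no time limit relative to the first dose and does not say which data the committee sees.

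The surrounding facts are these:
- Study Design: single arm, open label, with screening of up to 7 days.
- Introduction: diagnosis is by ruling out other causes. On test timing, counted from presentation, it says: "definitive test results (autoantibodies or genetic testing), which are only positive in approximately 60% of patients, are not typically available for days to weeks".
- Safety Analyses: laboratory data are taken at every visit, including days 1, 7 and 14, then every two weeks to week 26.
- Introduction and Discussion: patients without complement-mediated disease may respond poorly. The Introduction adds that they may also resolve spontaneously.

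The decision rule is a single comparison with 30%: "A lower bound of the CI of ≥30% will demonstrate that iptacopan preserves a significant proportion of the treatment effect". The interval is "based on asymptotic Gaussian approximation with continuity correction method".

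**The concern.** Because the set already requires a dose, the exclusion sentence changes nothing for undosed patients. It has effect only when someone who has taken study drug is later found, or judged, ineligible. If the committee always ruled before the first dose, the committee half of the sentence would have nothing to act on.

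For such a patient, platelets, LDH and creatinine after dosing may already be known when the decision is made. The article gives the decision-maker a reason to read a failing response as evidence against the diagnosis. A patient removed in this way leaves both numerator and denominator. If removal is more likely for non-responders, the estimated response rate is too high, and so is the chance of passing 30% in the one confirmatory comparison. There is no control arm to absorb the bias, and the article describes no analysis of all dosed patients that would reveal it.

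**Working it through.** **Inputs.** Threshold 30%, two-sided 95% interval, success if the lower bound is at least 30% (Primary Efficacy Estimand). N = 50 (Sample Size Determination). The exclusion probabilities below are assumptions; the article gives none.

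**Interval.** With p = x/n, the limits are p ± [1.96 × √(p(1−p)/n) + 1/(2n)].

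**Reproducing the plan's figures.** At n = 50 and p = 0.5 the half-width is 0.1386 + 0.0100 = 0.1486, consistent with "The proposed sample size of 50 patients is sufficient to achieve a target absolute margin of error not larger than 0.15". The quoted historical intervals also reproduce: 23/41 gives 56.1% (39.7%, 72.5%) and 30/56 gives 53.6% (39.6%, 67.5%, to rounding). Those counts are inferred from the percentages. The formula is therefore the one the plan uses.

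**Step 1: the cut-off with all 50 kept.**
- 23/50: 0.4600 − 0.1381 − 0.0100 = 0.3119, pass.
- 22/50: 0.4400 − 0.1376 − 0.0100 = 0.2924, fail.

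**Step 2: removing non-responders only.**

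| Start | Removed | Analysed | Lower bound | Result |
|---|---|---|---|---|
| 22/50 | 1 | 22/49 | 0.2995 | fail |
| 22/50 | 2 | 22/48 | 0.3070 | pass |
| 21/50 | 3 | 21/47 | 0.2940 | fail |
| 21/50 | 4 | 21/46 | 0.3017 | pass |
| 20/50 | 7 | 20/43 | 0.3044 | pass |

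**Step 3: chance of success at a true all-dosed rate of 30%, fixed number removed, always non-responders.** This is the binomial tail for n = 50.
- None removed, at least 23 needed: 1.23%.
- Two removed, at least 22 needed: 2.51%.
- Four removed, at least 21 needed: 4.78%.

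**Step 4: random exclusion.** Let X ~ Bin(50, 0.30) be the responders. In the selective case, B ~ Bin(50 − X, q) non-responders are removed, and success means that the lower bound for X/(50 − B) is at least 0.30. In the unrelated case, every patient has the same chance q of removal. Summing exactly over all outcomes:

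| q (assumed) | Non-responders only | Unrelated to response |
|---|---|---|
| 0 | 1.2% | 1.2% |
| 5% | 1.9% | 1.3% |
| 10% | 3.1% | 1.4% |
| 20% | 6.4% | 1.3% |

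With 35 non-responders expected (0.70 × 50), q = 10% means about 3.5 removals and q = 20% about 7. Exclusion by itself does almost no harm to the error rate; dependence on response does.

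**The case against.** The strongest reply is that nothing in the article says the committee decides late or sees response. Confirming enrolment can be read as a pre-dose step, the review is called independent, and the central-laboratory route is objective. A charter or the full protocol may fix timing and access. This stands in part: use of outcome is inferred from silence. It does not remove the point, because the article itself states the rule for the primary population, and that rule has effect only after dosing. Independence is also not masking.

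The late-test argument is limited too. Key eligibility in Table 1 does not make a negative genetic or autoantibody result an exclusion, and a late finding of a listed genetic cause is a baseline fact. Excluding on such a fact, without sight of outcome, would not bias the estimate.

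The direction is not certain. The Introduction allows for spontaneous resolution in misdiagnosed patients, so removals may include responders. Nor is all of the increase in Step 4 necessarily false-positive error. Removing 10% of non-responders raises the rate among those left to 0.30/(0.30 + 0.63) = 32.3%. If those removed were truly ineligible, part of the 3.1% reflects a higher rate in the intended population.

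A reader might infer that two removals can generally rescue a failed trial. They do so only at exactly 22 of 50, which has probability 1.3% at a true 30% and 7.9% at a true 50%. Because the continuity-corrected rule is conservative, two selective removals bring the error only to about the planned one-sided 2.5%.

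A reader might also infer that the 30% threshold is too low. The plan calls its sources "2 historical trials that are comparable in study design, population, and efficacy endpoints", while the Discussion says of the ravulizumab trial that there were "a number of patients enrolled who did not appear to have complement-mediated aHUS". The documents do not support that step. They give no count of such patients and no response rate among them. The eculizumab trial, described as having a high mutation-positive rate, has almost the same lower bound (39.7% against 39.6%). The ravulizumab rate fits 30/56, whereas the Discussion counts 58 patients, so it may itself come from a reduced set.

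**Conclusion.** The point holds as a weakness in how the primary analysis population is defined. The rule removes dosed patients in an open-label, single-arm trial without tying the decision to pre-dose information or masking it to response. Outcome-related exclusion is therefore possible, with bias most plausibly upward. The article does not show that it will happen.

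The size depends on the assumption. At a true 30%, success moves from 1.2% to 3.1% if non-responders alone have a 10% chance of exclusion, and stays at about 1.2% to 1.4% if exclusion is unrelated to response. With selective removal of a fixed number, about four are needed before the error clearly exceeds 2.5%. The observed result is fragile only near the cut-off: two removals at 22/50, four at 21/50. No conclusion about the 30% benchmark follows. This should be fixed; confidence is moderate, because a charter or full protocol that is not shown may already contain the safeguard.

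**What to change.** Amend the full-analysis-set text so that a dosed patient may be excluded only on data or samples obtained before the first dose. The decision should be dated and made without access to post-dose platelets, LDH, creatinine, dialysis or rescue data. It should cover both the central-laboratory and the committee route.

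Pre-specify an analysis of all dosed patients against the same 30%, reported beside the primary result. Use observed response status where it exists, in line with the estimand's use of all available data after treatment discontinuation. Add a version that counts every excluded dosed patient as a non-responder as the conservative bound. That version should not stand alone, since it discards observed responses.

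The cost is a paragraph in the protocol and committee charter and one extra analysis with two scorings. The all-dosed result may be less favourable than the primary. If the charter already contains these limits, only the text has to be aligned.

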#### Interim Analysis

An interim analysis will be performed when approximately 8 patients have completed 12 weeks of study treatment (day 84 visit). The intent of the interim analysis is to provide preliminary evidence on the efficacy and safety of iptacopan in treatment-naïve patients with aHUS. The interim analysis will include analysis of the primary end point (complete TMA response) at 12 weeks and its components (hematological normalization [platelet count and lactate dehydrogenase]), improvement in kidney function ([≥25% serum creatinine reduction from baseline]) as well as hematological parameters (platelets, lactate dehydrogenase, hemoglobin) and kidney outcomes (glomerular filtration rate and dialysis requirement) relevant to clinical benefit in patients with aHUS.

#### Safety Analyses

Patient safety will be closely monitored by investigators at prescreening, on days 1, 7, and 14, then at biweekly visits until 26 weeks, and monthly visits thereafter. At each visit, physical examination, vital signs (blood pressure, heart rate, pulse rate, respiratory rate, pulse oximetry), and body temperature will be assessed. Electrocardiograms will be recorded at selected visits and laboratory data will be measured at all visits.

Treatment-emergent adverse events, death, serious adverse events, and other significant adverse events, including those leading to treatment or study discontinuation will be summarized by primary system organ class and preferred term.

The use of prespecified rescue medications are not included in the protocol and will be selected at the discretion of the investigator based on local guidelines and availability.

#### Biomarkers

Blood and urine samples will be collected on days 1, 28, and 182; and analyzed for Wieslab AP, Factor Bb fragments and sC5b-9 at each of the 3 visits. These results will be used to determine if baseline levels change with treatment and predict patient outcomes and/or renal disease progression.

#### Sample Size Determination

The proposed sample size of 50 patients is sufficient to achieve a target absolute margin of error not larger than 0.15 (half-width of a 2-sided 95% CI for the proportion of patients reaching the status of responder) based on asymptotic Gaussian approximation with continuity correction method.

Under the assumption of the true TMA response rate for patients treated with iptacopan being 50%, at 1-sided alpha of 2.5%, the sample size of 50 will provide >80% probability that 2-sided 95% CI will exclude TMA response rate of 30%.

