## Methods

### Study Population

Approximately 50 patients naïve to complement inhibitors (including anti-C5 antibody therapy) will be enrolled. All patients are to provide written consent and fulfill all the inclusion criteria and not meet any of the exclusion criteria (Table 1).

**Table 1 tbl1:** Key inclusion and exclusion criteria

Inclusion	Exclusion
Aged ≥18 yrs	Treatment with complement inhibitors, including anti-C5 antibody
Evidence of TMA, including thrombocytopenia, evidence of hemolysis, and acute worsening of kidney function	ADAMTS13 deficiency (<10% activity)
	Shiga toxin-related HUS
	Positive direct Coombs test
Vaccination against *Neisseria meningitidis, Streptococcus pneumoniae* and *Haemophilus influenzae*	Known diacylglycerol kinase mediated HUS
	Identified drug exposure-related HUS
	HUS related to known genetic defects of cobalamin C metabolism
Patients with a kidney transplant are permitted; however, must: (a) have a known history of aHUS before current kidney transplantation, or (b) have no known history of aHUS, and persistent evidence of TMA at least 4 days after modifying the immunosuppressive regimen	Receiving plasma exchange/plasma infusion for ≥28 days before the start of screening for the current TMA
	Bone marrow/hematopoietic stem cell transplantation, heart, lung, small bowel, pancreas, or liver transplantation
	Patients with sepsis, severe systemic infection, COVID-19 infection, systemic infection which confounds an accurate diagnosis or impedes management of aHUS,
	Patients with a history of recurrent invasive infections caused by encapsulated bacteria
	Systemic sclerosis, systemic lupus erythematosus or antiphospholipid antibody positivity or syndrome, or any other autoimmune disease associated with HUS
	Chronic hemodialysis or peritoneal dialysis

ADAMTS13, a disintegrin and metalloproteinase with a thrombospondin type 1 motif, member 13; HUS, hemolytic uremic syndrome; TMA, thrombotic microangiopathy.

Other protocol-defined inclusion/exclusion criteria may apply.

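### For the 30% success rule, the continuity-corrected Gaussian interval never needs fewer responders than the Clopper-Pearson interval and at some analysis-set sizes near 50 needs one more, costing about 8 to 10 points of power

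*Protocol article*

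**What the plan says.** Under Primary Efficacy Estimand, the protocol article compares the response rate with 30% through a two-sided 95% interval, "based on asymptotic Gaussian approximation with continuity correction method". Success is a lower limit of 30% or more. The two historical response rates behind the 30% threshold are shown with the same type of interval.

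Under Sample Size Determination, 50 patients are described as "sufficient to achieve a target absolute margin of error not larger than 0.15", where the margin is the "half-width of a 2-sided 95% CI for the proportion of patients reaching the status of responder". The same section claims more than 80% power to exclude 30% if the true rate is 50%, at one-sided 2.5%.

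Two statements bear on how many patients will be analysed. Study Population says: "Approximately 50 patients naïve to complement inhibitors (including anti-C5 antibody therapy) will be enrolled". The full analysis set paragraph under Primary Efficacy Estimand says that patients found ineligible by the central laboratory, or "not confirmed to be eligible by the patient selection committee will be excluded from the full analysis set".

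**The concern.** The interval method is fixed in the article and decides a single-arm pivotal trial, so its behaviour at the 30% boundary matters more than its general properties. A continuity-corrected Gaussian interval is an approximation. The Clopper-Pearson interval is exact and guarantees a one-sided error of at most 2.5% at any n. If the approximation also asks for more responders at some sizes, the trial gives up power there and gains only error control stricter than the 2.5% the article allows.

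The size of the analysis set is uncertain because enrolment is approximate and exclusions are foreseen. The sponsor cannot know in advance whether it will land on a size where the two rules agree.

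**Working it through.** **Inputs.** From Primary Efficacy Estimand: threshold 0.30, two-sided 95% interval, success if the lower limit is at least 0.30. From Sample Size Determination: n = 50, true rate 0.50, one-sided alpha 0.025, margin 0.15. Assumed: n = 44 to 52 for the analysis set, because the article gives no number of exclusions.

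**Formulas.** With x responders among n and p = x/n:
- Corrected Gaussian: p ± [1.96·√(p(1−p)/n) + 1/(2n)].
- Clopper-Pearson lower limit: the 0.025 quantile of Beta(x, n−x+1). Upper limit: the 0.975 quantile of Beta(x+1, n−x).
- Cutoff c: the smallest x whose lower limit is at least 0.30. Power = P(X ≥ c) at rate 0.50; error = P(X ≥ c) at rate 0.30; both exact binomial.

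**The article's own margin.** At n = 50 and p = 0.5: 1.96·√(0.25/50) + 1/100 = 0.1386 + 0.0100 = 0.1486. The stated 0.15 is reproduced. The formula also returns the two historical intervals with counts of 23/41 and 30/56. These counts are inferred from the printed percentages and limits and are not given in the article.

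**Cutoff, power at 50% and error at 30%.**

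| n | Gaussian: cutoff, power, error | Exact: cutoff, power, error |
|---|---|---|
| 44 | 21, 67.4%, 1.00% | 20, 77.4%, 2.18% |
| 45 | 21, 72.4%, 1.35% | same |
| 46 | 21, 76.9%, 1.80% | same |
| 47 | 22, 72.0%, 1.12% | 21, 80.9%, 2.35% |
| 48 | 22, 76.5%, 1.48% | same |
| 49 | 23, 71.6%, 0.92% | 22, 80.4%, 1.95% |
| 50 | 23, 76.0%, 1.23% | same |
| 51 | 23, 80.0%, 1.61% | same |
| 52 | 24, 75.6%, 1.02% | 23, 83.4%, 2.09% |

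Example at n = 49 with 22 responders: the Gaussian lower limit is 0.2995 (fail) and the exact lower limit is 0.3067 (pass). At n = 50 with 22 responders both fail, the exact one narrowly (0.2924 and 0.2999), so both need 23.

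Over n = 30 to 80 the exact cutoff is one lower at 22 of the 51 sizes, equal at the other 29, and never higher.

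**Worst half-width over all outcomes.**

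| n | Gaussian | Exact |
|---|---|---|
| 50 | 0.1486 | 0.1447 |
| 49 | 0.1502 | 0.1462 |
| 48 | 0.1519 | 0.1477 |
| 47 | 0.1536 | 0.1493 |
| 46 | 0.1554 | 0.1510 |
| 45 | 0.1572 | 0.1526 |

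**Historical lower limits by the exact method** (inferred counts): 23/41 gives 39.7% and 30/56 gives 39.7%. The reference of about 40% behind the threshold is unchanged.

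**The case against.** The case for leaving the method alone has real parts.

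- *The quoted margin is correct.* It is promised for 50 patients and holds there for every outcome. A reader might infer that it breaks once one patient is excluded. At n = 49 the excess is 0.0002, occurs only at 24 or 25 responders, and rounds to 0.15. No decision depends on it. This stands, and the margin is a secondary point.
- *The Gaussian interval is not worse in every respect.* A reader might infer that the exact interval always dominates. It does not: at 30/50 the Gaussian lower limit is 0.4542 against 0.4518, and at n = 50 the Gaussian interval is narrower at 1 to 3 and 47 to 49 responders. The comparison holds only for the 30% success rule.
- *No power is lost at the planned size.* At n = 50 both rules need 23 responders, with identical power and error. This stands. The loss depends on which n is reached.
- *The number excluded is unknown.* The selection committee also confirms enrolment, so some ineligible patients may never count among the 50. Replacement or over-enrolment rules may sit in the full protocol, which is not shown. The article therefore does not establish that exclusions were left without allowance. It does establish that the analysed number need not be 50.
- *The stricter cutoff is conservative, not invalid.* This is true: the Gaussian rule keeps its error below 2.5% at every size in the table. But the article already accepts 2.5%, and the exact rule stays inside it.
- *The method matches the historical intervals.* The match is kept if those intervals are recomputed the same way, and their lower limits hardly move.

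**Conclusion.** The point holds as a matter of efficiency, not validity. For the 30% comparison the continuity-corrected Gaussian rule is never easier to meet than the Clopper-Pearson rule for n = 30 to 80. Within the assumed range of 44 to 52 it is harder at four sizes (44, 47, 49, 52), at a cost of 7.8 to 10.0 points of power if the true rate is 50%. At the other five sizes, including 50, there is no difference.

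The change would not rescue the power claim. At n = 50 power is 76.0% by either method, below the more than 80% that Sample Size Determination states, so that figure has to be restated whichever interval is kept.

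The conclusion rests on the article's true rate of 50% and on the assumed range of analysis-set sizes.

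**What to change.** Before the data are analysed:

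1. Name the Clopper-Pearson 95% interval for the primary comparison with 30%.
2. Show the two historical intervals by the same method. Their lower limits stay near 40%.
3. Restate the planning figures on the full analysis set: worst half-width 0.145 at n = 50, at most 0.15 down to n = 47, and 0.153 at n = 45; power 76.0% at n = 50 if the true rate is 50%.

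The cost is a line of text and recalculated figures, with no extra patients. The downside is that, where the rules differ, the false-positive rate at a true rate of 30% rises from about 1% to about 2%, still within the stated 2.5%.

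### The stated power above 80% does not follow from the plan's own decision rule: with the continuity-corrected interval, 50 patients give 76% power at a true response rate of 50%

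*Protocol article*

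**What the plan says.** The Primary Efficacy Estimand section sets the decision rule. "The calculated TMA response rate will be compared with a threshold of 30" (percent), by means of a two-sided 95% interval "for the proportion of complete TMA responders in iptacopan-treated patients based on asymptotic Gaussian approximation with continuity correction method". Success is a lower limit at or above that threshold: "A lower bound of the CI of ≥30% will demonstrate that iptacopan preserves a significant proportion of the treatment effect".

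The Sample Size Determination section justifies 50 patients in two ways. The first is precision: "The proposed sample size of 50 patients is sufficient to achieve a target absolute margin of error not larger than 0.15", with the same continuity-corrected method named. The second is power. "Under the assumption of the true TMA response rate for patients treated with iptacopan being 50" (percent), and "at 1-sided alpha of 2.5" (percent), it claims that "the sample size of 50 will provide >80% probability that 2-sided 95% CI will exclude TMA response rate of 30" (percent). The power statement names no other interval.

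**The concern.** The article gives everything needed to check the power claim: sample size, assumed rate, threshold, alpha, interval method and success rule. A continuity correction widens the interval by 1/(2n) on each side, which is one percentage point at n = 50. That is enough to change how many responders are needed, so a power figure that ignores it would be too high.

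This is the only power statement for the primary endpoint of a study that the Discussion calls pivotal. If it is wrong, readers, the sponsor and anyone judging the adequacy of the sample size are working with too low a risk of failure at the planned effect.

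**Working it through.** **Inputs.** From Sample Size Determination: n = 50, true rate 0.50, one-sided alpha 2.5% (z = 1.96). From Primary Efficacy Estimand: threshold 0.30, success if the lower limit is at least 0.30, Gaussian interval with continuity correction.

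**Which corrected interval is meant.** The natural reading is p ± 1.96·√(p(1−p)/n) ± 1/(2n). The historical intervals that the article prints under the same method name can test this reading. The denominators are not printed; the counts 23/41 and 30/56 are inferred from the percentages.

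- 23/41 = 56.1%: half-width 0.1519 + 0.0122 = 0.1641, giving 39.7% to 72.5%, as printed. Without correction it would be 40.9% to 71.3%.
- 30/56 = 53.6%: half-width 0.1306 + 0.0089 = 0.1395, giving 39.6% to 67.5%, as printed. Without correction it would be 40.5% to 66.6%.

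The article's own figures therefore fit this form.

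**Reproducing the stated figure.** The claim of more than 80% is met when the correction is left out:

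- Standard error at 0.50: √(0.25/50) = 0.0707.
- Normal approximation: Φ(0.20/0.0707 − 1.96) = Φ(0.868) = 80.7%.
- Exact: at 22/50 the uncorrected lower limit is 0.44 − 0.1376 = 30.2%, which passes. P(X ≥ 22 | 50, 0.50) = 83.9%.

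**The planned interval.** Lower limit = p − 1.96·√(p(1−p)/50) − 0.01.

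| Responders | p | 1.96·SE | Lower limit | Result |
|---|---|---|---|---|
| 22 | 0.44 | 0.1376 | 29.2% | fails |
| 23 | 0.46 | 0.1381 | 31.2% | passes |

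- Exact power: P(X ≥ 23 | 50, 0.50) = 76.0%.
- Normal approximation: Φ((0.20 − 0.01)/0.0707 − 1.96) = Φ(0.727) = 76.6%.
- Exact one-sided error at 0.30: P(X ≥ 23 | 50, 0.30) = 1.2%.

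**Sensitivity to the true rate (n = 50, 23 needed).** Exact power is 80.2% at 51%, 83.9% at 52% and 92.2% at 55%. At the historical rates of 53.6% and 56.1% it is 88.9% and 94.3%.

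**Sensitivity to n (true rate 50%, planned interval).** Exact power moves in a sawtooth because the critical count is an integer: 79.9% or 80.0% after rounding at n = 51 (0.7995), 75.6% at 52, 83.0% at 54, 79.1% at 55 and 82.5% at 56. It stays above 80% from 56 up to 65, the largest n checked.

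**The precision claim.** The maximum half-width at n = 50 is 0.1386 + 0.01 = 0.1486, so the 0.15 target holds under the corrected method.

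**The case against.** The strongest objection is that the power sentence stands in its own paragraph, does not repeat the interval method, and refers to a one-sided alpha, so it may come from a standard one-sample test of a proportion. Two methods that keep a continuity correction also exceed 80%. A corrected normal-approximation test using the variance at 30% gives 81.3%. A corrected Wilson interval has a lower limit of 30.3% at 22/50, so 22 responders suffice and exact power is 83.9%. This stands in part. The document does not show how the figure was obtained, and omitting the correction is only one possible route. It does not rescue the claim, because neither method is the interval that decides the trial, and the printed historical intervals fit the simple corrected Gaussian form.

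The second objection is about weight, and it largely stands. The gap is one responder and about four points below 80%, and part of it is the discreteness of the binomial at exactly 50, while the article says only that approximately 50 will be enrolled. The corrected rule is conservative: 1.2% one-sided error, where a cut-off of 22 would give 2.51%. The error cannot produce a false claim of efficacy, and power is about 89% to 94% if iptacopan matches the historical rates.

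It is also fair to say that a smaller full analysis set does not illustrate this defect. At n = 45 both the corrected and the uncorrected interval need 21 responders, and power is 72.4% either way.

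**Conclusion.** The power statement is wrong as written. Under the interval and success rule in the Primary Efficacy Estimand section, 50 patients give 76.0% power at a true rate of 50% (76.6% by normal approximation), against a stated value above 80%. The risk of missing the goal at the planned effect is 24%. A true rate of about 51% would be needed to reach 80%.

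This rests on 50 patients in the full analysis set and on the continuity correction being 1/(2n) applied to the simple Gaussian interval. The method's name and the historical intervals support that form, the latter at inferred counts. The estimand, the decision rule, type I error control and the 0.15 precision claim are unaffected. What is wrong is the stated probability of success.

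**What to change.** Replace the power sentence with one that matches the decision rule, for example: with 50 patients in the full analysis set, at least 23 responders are needed for the continuity-corrected lower limit to reach 30%; power is 76% at a true rate of 50%, 84% at 52% and 92% at 55%. Stating the critical count lets any reader check the figure.

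This costs one sentence and no patients; the stated power becomes slightly less favourable. There are two alternatives, both dearer. Keeping power above 80% at a true rate of 50% under the planned interval would take 54 patients (83.0%), or 56 to clear the dip to 79.1% at 55. Dropping the correction would change the primary decision rule and put the exact one-sided error at 2.51%, marginally above 2.5%. Restating the power is the cleaner choice.
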